## Abstract

**Background:**

Psychosis is a severe and disabling mental disorder with peak incidence in late adolescence and early adulthood. Following a first-episode psychosis (FEP), clinical trajectories diverge into affective psychoses or non-affective psychoses. At illness onset, differentiation between these trajectories is frequently impossible, which results in delayed treatment adaptation and increased relapse risk. Predictive biomarkers, particularly linguistic and inflammatory markers, may help refine early diagnosis and personalize care.

**Objective:**

The primary objective of the PEPAMARKER study is to develop a predictive model based on prosodic markers to identify affective *vs*. non-affective trajectories at 2-year follow-up of patients with first-episode psychosis.

**Methods:**

PEPAMARKER is a prospective, multicenter, minimal-risk study conducted in five psychiatric centers in France. A total of 217 participants aged 15–30 years with FEP will be enrolled and followed for 24 months. At baseline, data will be collected through clinical interviews (audio-recorded and transcribed), standardized rating scales, and inflammatory markers. Prosodic markers will constitute the primary predictors. Secondary predictors include syntactic/semantic features, inflammatory biomarkers, and clinical rating scales. The primary endpoint is affective *vs*. non-affective evolution of psychosis at 2 years. Statistical analyses and logistic regression models will be conducted along with the assessment of internal validity.

**Expected impact:**

The study aims to provide accessible predictive tools using clinical interview recordings and basic blood tests to improve early differentiation of psychosis trajectories, which is crucial to a timely treatment adaptation and a reduction in relapse risk.

**Clinical Trial Registration:**

https://clinicaltrials.gov/, identifier NCT05384392.

## Introduction

Psychosis is a frequent and severe mental disorder (1). Epidemiological data from the Social Epidemiology of Psychosis in East Anglia (SEPEA) study in England reported an incidence of 34 new cases per 100,000 person-years, and a peak between ages 16 and 19 was reported (2). Following a first-episode psychosis (FEP), two broad clinical trajectories can be observed: affective psychoses (approximately 17%) and non-affective psychoses (approximately 83%). A major clinical challenge is that at the onset of psychosis, it is often impossible to determine which trajectory a patient will follow. This diagnostic uncertainty delays adequate therapeutic decisions and increases the risk of relapses.

In recent years, advances in the field of computational psychiatry have had underscored the promise of linguistic biomarkers as potential predictors of illness trajectory (3–6).

Language production and comprehension allow interpersonal communication based on different linguistic components such as syntax, semantics, and phonology. When a speaker wants to express their thoughts, ideas, and/or feelings (semantics), they structure the necessary words (syntax) and utter the latter (phonology). A listener hears the sound and understands the utterance by processing the elements in the opposite direction (7). The study of language has the potential to provide a quantitative and objective measure of disorders. This approach has the advantage of acquiring a supplementary instrument in a non-invasive way to enhance the diagnostic and prognostic capabilities for patients afflicted with psychiatric disorders. The employment of machine learning facilitates a more sophisticated graphical analysis of language than that achievable with clinical scales (8, 9). Language deficits have been identified in a number of psychiatric disorders, most notably in patients suffering from mood disorders or schizophrenia (10).

As demonstrated by several studies, patients suffering from schizophrenia can experience difficulties finding the appropriate words to express themselves (11) and present lexical disorders (12). Their discourse is also often marked by disfluency, an abusive use of relative propositions (13), or abnormal prosodic features (14).

Specific speech characteristics of bipolar disorder remain a matter of debate (15). Some studies find general impoverishment of speech, with a lack of detail and references to oneself, especially during depressive phases (16).

Differences in language disorders affecting patients with mood disorders accompanied by psychotic features compared to those with non-affective psychoses can be shown. It is thus possible to identify linguistic markers for these pathologies (17). Some studies have found that alterations in syntactic structures and prosody could be more prevalent in psychosis than mood disorders with psychotic features (5, 18, 19). A study by Perlini et al. also suggested that syntax and verbal abilities were impaired in both affective and non-affective psychoses, but more frequently and severely in schizophrenic disorders (20). Illogicality would be a key difference between schizophrenic disorder and bipolar disorder (17). A systematic review emphasized the value of natural language processing (NLP) and machine learning in mental health prediction (8).

In parallel, biological markers have emerged, notably inflammatory markers. An immune dysfunction manifested by an increase in pro-inflammatory biomarkers and a decrease in anti-inflammatory biomarkers may be involved in the pathogenesis of psychiatric disorders in some individuals (21). Numerous studies have shown that depression, bipolar disorder, and schizophrenia are associated with immune response dysregulation. Metabolic syndrome is highly prevalent in schizophrenia, bipolar disorder, and major depressive disorder and may exacerbate or modulate inflammatory dysregulation. A large meta-analysis reported markedly elevated rates of metabolic syndrome across psychotic and mood disorders (22). In bipolar disorder, metabolic syndrome and its component factors have been shown to significantly influence the longitudinal course of illness, including relapse risk, chronicity, and functional outcomes (23). More recently, metabolic alterations have been linked to the activation of the kynurenine pathway and downstream inflammatory cascades in schizophrenia (24), further supporting the hypothesis that immune dysfunction in psychosis is embedded within a wider metabolic imbalance. It is also broadly documented that chronic inflammatory diseases are associated with a high rate of psychiatric comorbidity (25–27), frequently with an impact on mood (28). Finally, it is noteworthy that several antipsychotics and mood stabilizers have intrinsic anti-inflammatory properties (29).

The serum levels of inflammatory cytokines are elevated in individuals suffering from a major depressive disorder: increased levels of alpha cytokines TNF-α (tumor necrosis factor α), interleukin-6 (IL-6), and interleukin-1 beta (IL-1 β) (30, 31). A meta-analysis from 2011 (29) showed that cytokine levels did not decrease, even when patients experienced an improvement in their mood symptoms.

Some pro-inflammatory cytokines may also increase in patients with bipolar disorder. These include C-reactive protein (CRP), IL-1β, soluble interleukin-2 receptors (sIL2R), interleukin-4 (IL-4), IL-6, TNF-α, and TNF-α type 1 receptor (32). It has also been reported that the serum levels of these cytokines are mood dependent. Thus, high serum concentrations of IL-4, IL-6, TNF-α, sTNFR1 (soluble tumor necrosis factor receptor-1), CXCL10 (CXC motif chemokine ligand 10), and CXCL11 (CXC motif chemokine ligand 11) are observed in manic phases. Similarly, high serum concentrations of IL-6, IL-1β, CRP, TNF-α, sTNFR1 and CXCL10 are also found in depressive phases (33, 34). IL-6 and TNF-α levels appear to be directly correlated with disease severity (35).

Meta-analyses have shown that patients experiencing a first-episode psychosis and chronic psychosis have elevated blood levels of cytokines (36), including soluble interleukin-2 receptor (sIL2R), IL6, interleukin-8 (IL8), interleukin-10 (IL10), interferon-γ (IFNγ), transforming growth factor-β (TGFβ), TNFα, CRP, and hyperleukocytosis (37, 38). Recent findings support the hypothesis of distinct immuno-inflammatory profiles across FEP trajectories (39).

Within this context, the PEPAMARKER study seeks to combine clinical, linguistic, and biological data to build a predictive model of psychosis trajectory after a first episode. Early differentiation of affective trajectories would enable better targeted pharmacological and psychosocial interventions, which most likely reduces relapse rates and improves long-term functional outcomes (40).

## Methods and analysis

### Study design

The PEPAMARKER is a multicenter, prospective cohort study conducted in five psychiatric centers in France. The study is categorized as minimal risk and little constraint, in compliance with the French and international Good Clinical Practice guidelines. Based on Riley et al. (41), 217 participants are required to achieve sufficient statistical power to develop a multivariable prediction model with three candidate predictors, assuming 17% affective psychoses (2) and expected *R*² of 0.3 (42, 43). Participants with first-episode psychosis (FEP) will be included and followed for 24 months, with assessments at baseline, 12 months, and 24 months.

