### Risk assessment

A methodological risk analysis was conducted to identify potential sources of bias in this multicenter prospective study. Selection bias may occur due to the inclusion and exclusion criteria, which could limit the representativeness of the broader first-episode psychosis population; this risk is mitigated through consecutive recruitment across centers using homogeneous eligibility procedures. Measurement bias is possible in both clinical assessments and speech-related measures, given differences in interviewing conditions, rather interpretation, or audio quality. To reduce this variability, all assessments rely on standardized scales administered by trained clinicians, and recorded interviews follow a uniform procedure, with biological samples processed according to established protocols in the certified biobank. Attrition bias is another anticipated challenge given the 24-month follow-up; the protocol allows a 12-month telephone visit and collects any available clinical information to limit missing diagnostic outcomes. Differences between centers may also introduce heterogeneity in patient profiles or clinical practices; this is addressed through harmonized procedures, central transcription of interviews, and regular monitoring ensuring adherence to the protocol. Finally, confounding factors such as psychotropic treatments, baseline symptom severity, or socio-demographic characteristics are documented systematically and will be accounted for in multivariable statistical modeling. The combination of these measures is intended to mitigate the primary methodological risks while maintaining the ecological validity of the study conducted in routine clinical settings.

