## Discussion

The PEPAMARKER study addresses one of the central challenges in early psychosis care: the difficulty of distinguishing affective trajectories. Early differentiation is crucial, as treatment strategies and prognoses differ substantially between these subgroups.

A major strength of this study is its multimodal approach, combining clinical interviews, linguistic analyses, and inflammatory biomarkers. While linguistic markers have already shown promise in distinguishing between schizophrenia and bipolar disorder (5, 6), their predictive value in real-world FEP cohorts remains to be established. Similarly, inflammatory markers have been reported to differentiate affective psychoses (39).

Another strength lies in the ecological design: assessments are based on routine clinical interviews and simple blood tests, ensuring feasibility and acceptability in everyday psychiatric practice. The sample size (217 patients across the five centers) makes it possible to develop a robust multivariable predictive model (41).

Several limitations must, however, be acknowledged. First, the study only includes French-speaking participants. As linguistic markers are language-dependent, the predictive characteristics identified in French may not be generalizable to other languages. Second, the naturalistic type/kind/character of the cohort implies heterogeneity of treatments during follow-up, which may induce variability. The study also carries a risk of follow-up losses, as visits are spaced out over 2 years in a population often at the beginning of their care pathway where building a therapeutic alliance is a major challenge. Furthermore, the question of how inflammatory markers evolve over time may arise, as these are recently identified indicators that are still being explored scientifically. Another limitation relates to the symptomatology of first-episode psychosis and the fact that the patients included are not yet receiving treatment—that is, some patients may call into question their ability to consent or to be present for the initial assessments. This doubt or uncertainty likely exposes them to a selection bias, as the most severe forms are often treated immediately. From an ethical standpoint, it is worth mentioning the risk of de-subjectification of the patient, with the fear of a loss of clinical meaning in favor of computational approaches (56). Finally, other potential predictors such as brain imaging (57) are not included.

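### The 217 participants stated as required are also the 217 to be enrolled, so any of the anticipated 24-month losses puts the number with an observed outcome below the requirement

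*Protocol article*

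**What the plan says.** Study design in the protocol article states that "217 participants are required to achieve sufficient statistical power to develop a multivariable prediction model with three candidate predictors". It names a published set of sample-size criteria for prediction models and gives the inputs as 17% affective psychoses and an R² of 0.3. The margin, the shrinkage target and the type of R² are not stated.

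The abstract (Methods) uses the same number for recruitment: "A total of 217 participants aged 15–30 years with FEP will be enrolled and followed for 24 months". The Discussion repeats it: "The sample size (217 patients across the five centers) makes it possible to develop a robust multivariable predictive model".

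The primary outcome is affective versus non-affective evolution at 2 years. On follow-up, Risk assessment says: "Attrition bias is another anticipated challenge given the 24-month follow-up". The limitations in the Discussion also name losses over the two years as a risk. The response is a telephone option at 12 months and the use of whatever clinical information can be obtained. No loss rate is given, and no step from a required to an enrolled number.

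**The concern.** A prediction model for a 24-month diagnosis is fitted on patients whose 24-month diagnosis is known. A required number from such a method therefore counts patients with an observed outcome. If the number enrolled is the same, the requirement is met only at zero loss, and the document itself does not expect zero loss.

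At stake is the accuracy of the central design statement. Readers are told that the study has the size it needs, described as power, when the enrolled number will deliver somewhat less than the criterion that appears to have set it.

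**Working it through.** **Inputs from the protocol article.** Outcome proportion 0.17, three candidate predictors, R² 0.3, required number 217 (all Study design); enrolled number 217 (abstract and Discussion).

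**Inputs assumed, because the document does not give them.** The method's usual defaults: margin ±0.05 on the overall proportion, shrinkage 0.9, optimism in R² 0.05, mean absolute prediction error 0.05. Loss by 24 months: 10, 20 or 30%.

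**Step 1: reproduce 217.** Precision of the overall outcome proportion:

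n = (1.96/0.05)² × 0.17 × 0.83 = 1536.64 × 0.1411 = 216.8, rounded up to 217.

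The match is exact, which leaves no room for an attrition allowance.

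**Step 2: the other criteria.** The maximum Cox-Snell R² at 17% is 1 − exp[2(0.17 ln 0.17 + 0.83 ln 0.83)] = 0.598. An R² of 0.3 on the Nagelkerke scale is then 0.3 × 0.598 = 0.179 on the Cox-Snell scale.

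Both overfitting criteria use n = P / [(S − 1) ln(1 − R²cs/S)] with P = 3. For shrinkage, S = 0.9. For optimism, S = R²cs / (R²cs + 0.05 × 0.598), which is 0.909 (Cox-Snell) or 0.857 (Nagelkerke).

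| Criterion | R² 0.3 as Cox-Snell | R² 0.3 as Nagelkerke |
|---|---|---|
| Shrinkage 0.9 | 74 | 135 |
| Optimism 0.05 | 83 | 90 |
| Mean absolute prediction error 0.05 (does not use R²) | 116 | 116 |
| Overall proportion ±0.05 (does not use R²) | 217 | 217 |

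The overall-proportion criterion is the largest under either reading, so it governs.

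**Step 3: what 217 enrolled delivers.** Evaluable n = 217 × (1 − loss); affective cases = 0.17 × n; margin = 1.96 × √(0.1411/n).

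| Assumed loss | Evaluable | Affective cases | Margin on the 17% |
|---|---|---|---|
| 0% | 217 | 37 | ±5.0 points |
| 10% | 195 | 33 | ±5.3 points |
| 20% | 174 | 30 | ±5.6 points |
| 30% | 152 | 26 | ±6.0 points |

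**Step 4: reserve on the overfitting criteria.** At 30% loss, 152 evaluable patients still exceed 135 and 83. The loss at which the larger overfitting requirement would fail is 1 − 135/217 = 38% (Nagelkerke) or 1 − 83/217 = 62% (Cox-Snell).

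**The case against.** The strongest reply is that the consequence is small. The criterion that sets 217 concerns the overall proportion, in effect the model intercept, and it slips by about one point at 30% loss. The stated objective is a predictive model, and the criteria that guard against overfitting keep a wide reserve. This stands, and it limits the severity.

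A second reply is that the plan already deals with losses. The statistical section says that all included patients are analysed by intention to treat, and Risk assessment describes ways to limit missing diagnoses. Collecting any available clinical information is not restricted to month 12 and may well recover some outcomes. But naming an analysis set does not supply a 24-month diagnosis, the telephone option is listed for month 12, and recovery would have to be complete to deliver 217.

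A third reply is that the ±5-point margin is inferred. That is true, and the authors should confirm it. The mismatch between required and enrolled numbers does not depend on it. Only the finding that 217 holds no allowance does, and there the exact match is strong evidence.

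A reader might go further and infer that quoting three predictors and R² 0.3 is itself an error, since neither enters the formula that gives 217. The document does not support that. The method evaluates several criteria and the largest governs; these are genuine inputs to it, and Study design never says that they were the binding ones. A reader might also want the effect expressed as a loss of precision in discrimination, or want unusable recordings added to the losses. The protocol article states no expected discrimination, and it mentions audio quality only as a source of measurement variability, so neither can be put in figures from the text.

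**Conclusion.** The point holds at moderate severity. Required equals enrolled, losses are anticipated in two places, and 217 appears to be an uninflated minimum. Any net loss takes the number with an observed outcome below the stated requirement. At assumed losses of 10 to 30%, the margin on the base rate moves from ±5.0 to between ±5.3 and ±6.0 points, with 33 to 26 affective cases instead of 37.

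The power wording is loose: the quantity that reproduces 217 is a precision target, not a power. It would be too strong to infer that the study is too small to develop its three-predictor model, because the overfitting criteria hold up to about 38% loss even on the less favourable reading of R².

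The conclusion rests on the assumed default margin, the assumed defaults for the other criteria, and a loss range that the document does not supply.

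**What to change.** Revise the abstract (Methods), Study design and the sample-size sentence in the Discussion so that they:

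- say that 217 is the number needed with an observed 24-month outcome;
- name the criterion and margin that set it (±5 points on a 17% proportion, if the authors confirm this);
- give the expected loss by 24 months, and the evaluable number, affective cases and precision that 217 enrolled will then deliver. If the sponsor expected 20% loss, for example, this would read 174 evaluable, about 30 affective cases and ±5.6 points;
- replace the power claim with that precision statement.

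The three predictors and the R² of 0.3 can stay as inputs. No extra enrolment is required. The cost is a change of wording, and the stated precision becomes slightly less favourable.

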### Participants

The inclusion criteria are as follows:

✔ Ages 15 to 30 years✔ Diagnosis of first-episode psychosis according to the DSM-5 criteria✔ Ability to provide informed consent (for minors, consent obtained from at least one legal guardian)

The exclusion criteria are as follows:

✔ Introduction or recent adjustment (within 1 month) of antipsychotic, antidepressant, or mood stabilizer treatment✔ Native language other than French✔ Psychosis due to an organic disorder✔ Substance-induced psychosis with severe dependence✔ Intellectual disability✔ Chronic inflammatory disease or immunomodulatory treatment: systemic inflammatory disorders (e.g., rheumatoid arthritis, lupus, inflammatory bowel disease, psoriasis), chronic inflammatory metabolic conditions (e.g., chronic type 2 diabetes with poor glycemic control, metabolic syndrome), and chronic inflammatory conditions linked to malignancy or chronic infections✔ Pregnancy or breastfeeding since these states have been shown to induce profound immunological and hormonal changes that strongly alter inflammatory cytokine levels (44)✔ Patients under guardianship, curatorship, or deprived of liberty

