### Outcomes

#### Primary outcome

• Affective *vs*. non-affective evolution of psychosis at 2 years based on prosodic markers at baseline:

Fundamental frequency (F0) variabilitySpeech latency (mean response time and coefficient of variation)

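### The promised tool is for patients whose trajectory cannot be told at onset, but the primary analysis pools them with any whose affective diagnosis is already evident at baseline

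*Protocol article*

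**What the plan says.** The rationale is diagnostic uncertainty. The Abstract (Background) states: "At illness onset, differentiation between these trajectories is frequently impossible". The Introduction says that "at the onset of psychosis, it is often impossible to determine which trajectory a patient will follow". Both statements are qualified, so they allow that the trajectory is clear early in some patients.

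The Objective in the Abstract is wider: a prosody-based model of the two-year trajectory in patients with first-episode psychosis, without restriction to uncertain cases. Participants follows the objective and requires "Diagnosis of first-episode psychosis according to the DSM-5 criteria". Among the exclusions are "Psychosis due to an organic disorder", substance-induced psychosis with severe dependence, "Introduction or recent adjustment (within 1 month) of antipsychotic, antidepressant, or mood stabilizer treatment", and patients deprived of liberty. Capacity to consent is required. No criterion refers to whether the affective question is still open at baseline.

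The Primary outcome is affective versus non-affective "evolution of psychosis at 2 years based on prosodic markers at baseline". Statistical analysis includes every enrolled patient, fits logistic regression on the prosodic markers, and assesses calibration and discrimination. Risk assessment adds that baseline symptom severity, among other factors, will be accounted for in multivariable modelling. The later part of the Discussion and the Dissemination plan present the expected product as a tool for early differentiation.

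**The concern.** A patient in a recognisable mood episode with psychotic features and a patient whose picture cannot yet be classified can both enter, and both count equally in the cohort-wide discrimination. If the first kind is common among the affective cases, good discrimination may show mainly that prosody picks up a current mood state.

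The article gives reason to think this possible. It lists speech rhythm and quantity among the manic symptoms rated by the YMRS, and the Introduction mentions impoverished speech in bipolar disorder, especially in depressive phases. The primary predictors, F0 variability and response latency, are close to these features.

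At stake is the final claim. A model could perform well overall and still add nothing in the undifferentiated patients for whom the tool is wanted, and no result described in the article would show the difference.

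**Working it through.** **The plan's own figure.** Study design gives 217 patients, 17% affective, three candidate predictors and R² 0.3. With the conventional margin of ±0.05 for the overall risk (not stated in the article), (1.96/0.05)² × 0.17 × 0.83 = 216.8, so 217. The other two criteria of the cited method require fewer: 135 and 90 if R² is Nagelkerke's, 74 and 83 if Cox–Snell's. The sample size reproduces and is not in question. Expected affective cases: 217 × 0.17 = 36.9. The Introduction gives this 17% for first-episode psychosis as a whole, so the 36.9 events include evident and undifferentiated cases together.

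**Effect of pooling.** I use the AUC as the discrimination index; the article names none. With one shared non-affective comparison group, the cohort AUC is the event-weighted mean:

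AUC(cohort) = s × AUC(evident) + (1 − s) × AUC(undifferentiated)

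Here s is the share of affective cases evident at baseline. The article gives neither s nor any AUC, so all values are assumptions: s = 0.3, 0.5, 0.7; AUC(evident) = 0.80 or 0.90; AUC(undifferentiated) = 0.50, deliberately the worst case. For example, 0.5 × 0.90 + 0.5 × 0.50 = 0.70. Undifferentiated events are 36.9 × (1 − s).

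The null standard error of the cohort AUC with 37 affective and 180 non-affective patients is √[218/(12 × 37 × 180)] = 0.052. The approximate chance that a two-sided 5% test finds the cohort AUC different from 0.5 is Φ[(AUC − 0.5)/0.052 − 1.96], using the unrounded standard error.

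| Share evident | Cohort AUC, evident 0.80 | Chance | Cohort AUC, evident 0.90 | Chance | Undifferentiated events |
|---|---|---|---|---|---|
| 30% | 0.59 | 41% | 0.62 | 63% | 26 |
| 50% | 0.65 | 82% | 0.70 | 97% | 18 |
| 70% | 0.71 | 98% | 0.78 | >99% | 11 |

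**Limit of this calculation.** It compares undifferentiated affective cases with all non-affective cases. A report within the undifferentiated group would compare them with undifferentiated non-affective cases only, which is a different AUC. The table shows what pooling can hide; it does not predict the subgroup result.

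**Precision of a subgroup report.** If the same share of non-affective patients is also evident, the undifferentiated group has about 26 v 126, 18 v 90 or 11 v 54 patients. The null standard error √[(n₁ + n₀ + 1)/(12 n₁ n₀)] is 0.062, 0.075 or 0.096, giving 95% half-widths of about 0.12, 0.15 or 0.19.

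**The case against.** The strongest reply is that eligibility matches the objective. The Objective is about first-episode psychosis as such, the Discussion speaks of real-world cohorts, and the 17% is the figure for all such patients. This stands. A reader might infer that the entry criterion is wrong and should be narrowed to uncertain cases; the article does not support that. The mismatch is between the analysis and the conclusion drawn from it.

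The exclusions also thin out evident cases. Recent start or adjustment of treatment, deprivation of liberty and inability to consent all bear most on florid presentations, and the Discussion notes that the most severe forms are often treated at once. This stands as a probable reduction, but none of these rules removes a patient because the diagnosis is clear, and Recruitment and consent still allows identification in hospital.

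Next, mood scales are taken at baseline, and Risk assessment promises to account for severity. That bears on whether prosody adds to current symptoms. But the promise is general, is not part of the primary model as described, names neither diagnosis nor its certainty, and does not change who is pooled.

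Finally, the full protocol, the eCRF and the analysis plan are not shown and may already hold a baseline diagnosis field or a subgroup report. That is a reason to check them first.

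**Conclusion.** The point holds as a gap between what the cohort-wide analysis can show and what the article expects to conclude. Pooling allows a cohort AUC of roughly 0.59 to 0.78 even if prosody has no value in undifferentiated affective cases. With half of the affective cases evident, such a result would differ from 0.5 with a chance of about 82% to 97%. These figures rest on an assumed share, assumed AUCs and a shared comparison group, and are illustrative only.

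A reader might go further and infer that a positive result will come from already evident patients, or that the tool merely detects current mood episodes. The article supports neither: it gives no share evident at baseline, and its exclusions probably lower that share. What it supports is that the planned result cannot tell these possibilities apart. The remedy is cheap and worth making, but the point does not undermine the design, the sample size or the primary analysis.

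**What to change.** Keep eligibility, the 217 patients and the cohort-wide primary analysis. Then:

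- Have the investigator code the working diagnosis at baseline in the eCRF as affective, non-affective or undifferentiated, before any marker is computed. The inclusion criterion already requires a DSM-5 diagnosis. For anyone already enrolled, take the code from what was recorded at inclusion, without knowledge of follow-up.
- Prespecify as a secondary analysis the discrimination of the primary model, with its confidence interval, in the undifferentiated group. Report calibration there only descriptively.
- Word the early-differentiation conclusion foreseen in the Discussion and the Dissemination plan according to that result. If the interval is too wide to decide, say that prediction was shown in the cohort and that its value in undifferentiated patients remains open.

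The cost is one eCRF field and one extra report. The estimate may rest on roughly 11 to 26 events, will be imprecise, and depends on an investigator's label whose reliability is unknown. For these reasons it should not replace the cohort-wide primary result.
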